# Evaluating community digital data linkage with or without community data use to increase antenatal care uptake in Western Kenya: protocol for a pragmatic open-label, cluster-randomised controlled superiority trial

**DOI:** 10.3389/frhs.2025.1697161

**Published:** 2026-01-27

**Keywords:** community referral, data linkage, digital health, electronic community health information systems, electronic medical records, quality improvement

## Abstract

**Background:**

Less than 10% of pregnant women in Sub Saharan Africa achieve the World Health Organization recommended eight antenatal care (ANC) contacts for optimal pregnancy management. Robust strategies that involve community outreach programmes, integrated service delivery and continuity of care could help improve ANC uptake and quality. Kenya, as other countries, has promoted use of digital health records at the community and facility levels to improve quality and access to data and promote continuity of care. These records, however, are not always linked and access to data does not guarantee its use to drive quality improvement. C-it-DU-it (pronounced “See it, Do it”) is a two-arm pragmatic cluster-randomised trial set in Homabay County, Kenya. The trial will implement digital linkage of community and facility electronic patient data (control arm) and assess the impact of having quality improvement teams reviewing and acting on the linked data (intervention arm). While several areas are captured in the community health records, we will focus on uptake of ANC services as a lens.

**Methods:**

Eighteen healthcare facilities (clusters) will be randomly allocated to either the control or intervention arms at a ratio of 1:1. A data linkage module will be deployed in all clusters, enabling digital referral of pregnant women between the community and health facilities. In each intervention cluster, work improvement teams will be established and trained on reviewing these electronic ANC data, identifying problems, developing and deploying context-specific solutions to these problems and evaluating the impact of their interventions. ANC data will be extracted for 1,440 recruited pregnant women. The primary outcome will be the proportion of pregnant women with at least eight ANC contacts. Secondary outcomes will be ANC uptake before 16 weeks gestation, adverse pregnancy outcomes, uptake of required investigations, medication and skilled birth attendance.

**Discussion:**

This trial intends to generate evidence on the benefit of community work improvement teams to review and act on linked digital data to develop and deploy solutions to local problems. This strategy, if successful, will promote antenatal service uptake and quality resulting in improved pregnancy outcomes and progress towards sustainable development goals if appropriately scaled up.

**Clinical Trial Registration**: https://clinicaltrials.gov/study/NCT05929586, identifier NCT05929586.

## Introduction

1

Sub Saharan Africa (SSA) carries the highest burden of maternal mortality, yet current estimates indicate less than 10% of the pregnant women meet the World Health Organization (WHO) target of eight antenatal care (ANC) contacts (1, 2). The Kenya Ministry of Health (MoH) adopted the WHO recommendation for eight or more ANC contacts in 2022 at a time when only 66% of the pregnant women in Kenya attained four or more ANC visits (3, 4). ANC attendance in low- and middle-income countries (LMICs), including SSA, is associated with reduced risk of neonatal mortality (5). Robust strategies are needed to improve ANC uptake if these and other benefits of increased uptake of skilled birth delivery and early postnatal care are to be achieved (6).

The WHO guidelines allow for context-specific variations on how the eight ANC contacts are achieved, including through community outreach programmes (3). Community-centred approaches such as community quality improvement (QI) have shown promise in strengthening community health systems in LMICs, particularly for maternal and child health outcomes (7). These QI interventions use a continuous QI model based on the “plan–do–study–act” cycle in which teams from the local community develop context-specific interventions which are tested and implemented after being proved to drive positive change (8, 9). This process is iterated to produce further improvements and the different QI teams share their learnings to promote best practice (9, 10).

A key component of QI approaches is access to reliable data to help identify gaps, set priorities and monitor progress in real-time (11). Digitisation of health data through introduction of electronic medical record (EMR) systems in healthcare facilities and community health information systems can provide more reliable and standardised data sources to support community QI initiatives (11). The Kenya MoH has been scaling up an electronic Community Health Information System (eCHIS) for Community Health Promoters (CHPs) in 2024 (12). This is a community health digital data capture tool designed to support household registration and service provision with in-built decision-support steps to facilitate referral to healthcare facilities and electronic reminders for community patient follow-up (12). In parallel, facility-based EMR systems, such as “KenyaEMR,” are being more widely used. The majority of these were initially used for vertical programmes such as HIV care delivery but may also support expanded use (antenatal care, delivery and postnatal care) (13). Community QI approaches that leverage these digital data systems could provide a robust health-systems-strengthening approach to improve ANC uptake and quality of care in Kenya and other LMICs.

The main barriers to attaining eight ANC contacts include financial constraints, rural residence, some religious affiliations and stigma towards unintended pregnancies (especially among adolescents). Others include cultural beliefs (such as pregnancies do n't need hospital attention), lack of partner support, distance to health facilities, high parity, lower level of education and delayed initiation of ANC (14–16). Context-specific interventions supported by accurate data, such as community QI initiatives leveraging digital health records, would afford robust strategies to improve ANC uptake in these circumstances. Evidence on these, however, is lacking as community health data digitisation at scale in SSA is a recent development.

C-it-DU-it (pronounced “see it, do it”) is a cluster-randomised controlled trial that will investigate the impact of having QI teams (subsequently referred to as “Work Improvement Teams” abbreviated as WITs) reviewing and acting on linked community and facility electronic data to improve ANC uptake.

## Methods and analysis

2

### Study aim

2.1

The C-it-DU-it trial aims to determine the impact on ANC uptake, ANC services and pregnancy outcomes of implementing WITs that use digitally linked data to identify and address local problems.

### Study sites

2.2

The trial will be conducted in Homabay County in western Kenya, on the southern shore of Lake Victoria, approximately 370 km from the capital Nairobi. It has a population of 1.13 million, of whom approximately 24% are women of reproductive age (17). Close to 20% of pregnant women in Homabay are aged below 19 years and common preventable conditions including malaria, HIV and anaemia are major contributors to adverse birth outcomes (18). The County was the first to scale-up EMR systems for HIV care in its healthcare facilities (KenyaEMR) and will be one of the counties in which eCHIS adoption is accelerated.

The trial will be conducted in randomly selected healthcare facilities across the County based on the following criteria:
Government or faith-based facilities with ANC clinicsFacilities located in Homabay County mainlandFacilities having at least 80 attended births per yearANC services linked with at least one fully functional community unit.Referral hospitals, facilities located in Homabay County islands of Lake Victoria, facilities with very limited access and/or seasonal impassability, facilities declining to participate (as communicated by the facility in-charge) and facilities currently involved in another study targeting pregnant women directly (patient-level interventions) or indirectly (health system interventions) will be excluded.

### Study design

2.3

This will be a two-arm, pragmatic, open-label, cluster-randomised superiority trial with 1:1 allocation of the arms.

### Control (C-it) arm

2.4

All CHPs and most ANC facility staff currently use paper-based registers and referral forms. Plans by the MoH to deploy linked electronic data capture systems nationally, however, means digital data capture will be the standard of care in the lifetime of the trial. The control arm will therefore have digital data capture as the “enhanced standard of care” as follows:
Electronic data capture by CHPs via eCHIS during household visits.Electronic data capture by ANC staff through use of the KenyaEMR Mother Child Health (MCH) module.A linkage module linking KenyaEMR and eCHIS.The county and sub-county health management teams will be supported by the trial team to distribute smart phones and ensure they are connected to the internet. They will work with the trial team to train CHPs in trial community units on the use of eCHIS for household registration, generation of National Unique Patient Identifier (NUPI), pregnancy mapping, patient referral and conducting household visits. NUPI refers to an identification number that will be generated from an individual's national ID or birth certificate number to enable linkage of an individual's clinical records across EMR systems. The same team will train ANC staff in trial sites on KenyaEMR MCH module to capture patient data, generate NUPI, identify community referrals and refer patients for community follow-up.

We will engage a software developer to design software in consultation with national and county health administration to link KenyaEMR and eCHIS records through the NUPI. This will enable longitudinal patient follow-up and prompts on eCHIS and KenyaEMR whenever a patient is referred. The software developer will offer technical support and address linkage errors such as NUPI mismatches in consultation with national and county health administration teams. We will train both CHPs and ANC staff at the facility on how to use the linkage module to anticipate and confirm completion of referrals. In order to comply with the Kenya Data Protection Act, we will implement additional access control measures including user authentication, role-based access and audit logs.

The use of eCHIS, KenyaEMR and the linkage app may be affected by system downtimes, electricity black-outs, disruption of internet access and loss or damage to equipment. To mitigate these, trial staff, ANC staff and CHPs will be trained to safely handle the equipment, troubleshoot and contact the right people when facing technical challenges. Since eCHIS roll-out will be country-wide, we anticipate provision for internet access for the CHPs to allow (near) real-time data uploads. Where not available, the trial team will provide back-up internet access within trial sites.

Finally, we will train both CHPs and facility staff on the trial definitions of community ANC contacts, the services offered to women in the immediate post-partum period and how to fill the trial CHP case report form (CRF) to document home visits. CHP training will include instructions on how to provide ANC-related services such as screening for danger signs, measuring blood pressure, mid-upper arm circumference and temperature, conducting pregnancy and malaria rapid diagnostic tests, and checking adherence to mebendazole, Iron and Folate Supplements and Intermittent Preventive Treatment for malaria in Pregnancy (IPTp). The CHP CRF will be attached to the MCH Book carried by the pregnant women.

### Intervention (C-it-DU-it) arm

2.5

Intervention sites will implement WITs in addition to adopting the enhanced standard of care (C-it). Each community unit will have one WIT comprising 3–4 CHPs, a Community Health Assistant (CHA), an ANC staff and/or the healthcare facility in-charge from the link facility (facility to which the CHPs refer patients from the community), a data clerk, an adolescent mother and a community representative. We will use a continuous QI model involving iterative cycles of developing and testing interventions with periodic collaborative sessions for sharing their innovations.

A five-person facilitation team [from Capacity Development International (CDI), LVCT Health and representatives from the sub-county and County Health Management Teams] will train the WITs in groups small enough to check learning and ensure fidelity to content. We will use a phased training approach, described in Figure 1, building on previous experience embedding QI into community health (9).

**Figure 1 F1:**
[figure not shown]
Summary of the phased WIT training model.

#### Building teams and measuring quality

2.5.1

The facilitation team and respective sub-county, facility and community unit leads will agree on WIT membership. They will orient WIT members on their roles, core QI concepts and agree on their terms of reference. They will discuss the changes in government policy from four to eight ANC contacts and the role of CHPs in early pregnancy identification and supporting pregnant women to achieve eight ANC contacts. They will train WITs on use of a community follow-up tool (9) to obtain insights into the quality of CHP community ANC visits.

There will be a 10-week interval during which WITs will sensitise link facility staff, CHPs and community members about their role in improving ANC uptake. CHAs will encourage regular household visits and assess eCHIS and CHP CRF data during monthly supervision meetings. The facilitation team will support the WITs to identify and train selected community volunteers to visit a sample of households to administer the community follow-up tool (9).

#### Analysing and using data to innovate

2.5.2

WITs will convene to share learning and experiences in implementing their action plans from the first training. The facilitation team will train WITs on use of tables, graphs and dashboards for data presentation and tracking of indicators while adhering to the Kenyan Data Protection Act 2019 (19). WITs will analyse eCHIS data, facility data and community follow-up tool data to identify and prioritise quality problems and develop a clearly defined problem statement. They will conduct a root cause analysis using the “Five-Whys?” technique (20) and brainstorm potential solutions with the aim of developing a change plan to address root causes. Sub-county health administration staff will be trained as WIT coaches.

There will be a 5–6-month interval during which WITs will implement and monitor their change plans. WITs will meet monthly to implement and refine their solutions, monitor core ANC indicators using their dashboards and prepare story boards to present to County officials during learning events. Coaches from the facilitation team and sub-county will offer mentorship to promote WIT team adherence to their mandate.

#### Sharing learning and good practice

2.5.3

Learning events will take place every 6 months and will convene all WITs, the facilitation team and county health administration. This will allow showcasing and rewarding of best practices and provide a forum for advocacy with higher levels of the healthcare administration system.

#### Definition of full implementation and embedding of the intervention

2.5.4

Full implementation will be assumed to occur after the training on analysing and using data to innovate is completed. Full embedding of the intervention will be assumed to occur 3–6 months after this. The intervention's earliest ANC contact likely to be impacted will deliver approximately 7–9 months after embedding (assuming ANC contact occurs in the first trimester). Outcome assessment (first patient-in) will therefore start 10 months after full implementation (Figure 2).

**Figure 2 F2:**
[figure not shown]
Summary flow diagram indicating project activities across arm and timelines. ANC, antenatal care; CHAs, community health assistants; CHPc, community health promoters; eCHIS, electronic community health information system; WIT, work improvement team, *N*, number of clusters; and *n*, number of participants.

### Relevant concomitant support

2.6

Routine supervisory activities by sub-county and county health management team members will continue in all sites during the implementation of the trial. The county staff are central to the design and delivery of the intervention and we will work with CHPs, facility staff and county health management without offering additional remuneration for implementing the enhanced standard of care or community QI.

### Cluster definition, randomisation and blinding

2.7

We will define a cluster as an ANC clinic meeting selection criterion, and this will be the unit of randomisation. An independent statistician will use a covariate-constrained randomisation approach to achieve balance across the two study arms. Specifically, we will apply the *l2* balance metric implemented in the “**cvrall**” package in R statistical software. All possible allocation schemes will be evaluated against predefined balance criteria, and a final allocation will be selected at random from a constrained set. A fixed random seed will be used to ensure reproducibility of the randomisation procedure. These covariates include sub-county, number of functional community units, number of CHPs, number of women of childbearing age, service provision level and the number of women attending four ANC visits and eight ANC visits.

We will convene the county and sub-county leadership, facility representatives and community representatives in a public event during which three County leaders will be asked to pick an unmarked sealed envelope containing details of allocation to a randomisation arm. We are unable to blind the allocation of arms given the nature of the intervention but will use a 5 km buffer zone between intervention and control facilities to minimise risk of contamination.

To minimise bias, we will use an objective primary outcome measure, and the statistician will be blinded regarding the allocation arm when the statistical analysis plan (SAP) is developed and analytical syntax is written. The actual allocation will only be provided to the statistician after locking the database and approval of the SAP by an independent Data Management Committee (DMC).

### Sample size and study endpoints

2.8

We conducted sample size calculations with consideration for the primary endpoint using Power Analysis Sample Size Software (PASS) v20 (21). The primary objective is to determine if C-it-DU-it is superior to C-it in increasing uptake of eight ANC contacts in western Kenya.

#### Primary endpoint

2.8.1

The primary endpoint will be the proportion of pregnant women attaining at least eight ANC contacts defined as either a scheduled ANC visit in the facility or a scheduled ANC contact with a CHP in the community assessed at birth (or within the first 6–8 weeks for home births). Community ANC contacts will be defined as a home visit that covers the elements of a community ANC visit plus at least one diagnostic test or the distribution of at least one drug. Diagnostic tests or drugs administered include pregnancy tests, malaria tests, iron and folate supplements, sulphadoxine-pyrimethamine, co-trimoxazole and mebendazole.

During a baseline survey, we estimated 3% of the pregnant women in Homabay achieved eight ANC contacts and deemed an increase to 12% would be the minimum effect size to warrant national scale-up of the intervention. To detect this four-fold increase in the primary outcome assuming an intra-cluster correlation coefficient (ICC) of 0.025, 90% power and an alpha of 0.05, a sample size of 1,024 women in 16 clusters (8 per arm) would be required giving an average cluster size of 64 women. To account for efficiency loss due to cluster size imbalance, we increased clusters to 9 per arm resulting in a total of 1,152 participants. To adjust for anticipated 20% loss to follow-up, we increased the sample size estimate to 1,440 participants in total (720 per arm) giving an average cluster size of 80 women. The sample size calculation will be reviewed and updated (if necessary) after completion of baseline data collection from 1,620 participants in trial sites to obtain an updated ICC. Baseline data collection will take place in the months during which WIT training and embedding of the intervention will occur, prior to recruitment of the first patient-in (Figure 3).

**Figure 3 F3:**
[figure not shown]
Implementation and participant timeline. The asterisk denotes baseline participant recruitment and follow-up will continue as the intervention is being implemented. eCHIS, electronic Community Health Information System.

#### Secondary objectives and endpoints

2.8.2

The secondary objectives are:
To determine if C-it-DU-it is superior to C-it on other secondary endpoints of ANC uptake. The endpoints are the proportion of women who had at least four scheduled ANC visits in the facility; the proportion of women who had at least eight scheduled ANC visits in the facility; the frequency of scheduled ANC visits in the facility; and the frequency of ANC visits in the community.To determine if C-it-DU-it is superior to C-it in increasing early ANC attendance with the endpoint of the proportion of women with a first ANC contact before 16 weeks gestation.To determine if C-it-DU-it is superior to C-it in improving the quality of ANC with the endpoints of the proportion of women who received at least three courses of IPTp-SP, iron and folate supplements for 90 days, testing and management for HIV, testing and management for malaria, testing and management for syphilis, and testing and management for anaemia.To determine if C-it-DU-it is superior to C-it in increasing uptake of skilled birth attendance with the endpoint being the proportion of women who had a skilled birth attendance.To determine if C-it-DU-it is superior to C-it in reducing the risk of adverse pregnancy outcomes with the endpoints being the proportion of women with a composite of foetal loss (stillbirth or spontaneous miscarriage), low birth weight or neonatal mortality.To determine if C-it-DU-it is superior to C-it in increasing uptake of week six childhood immunisation.

#### Exploratory endpoints

2.8.3

In addition, we included the following two additional exploratory endpoints:
To determine if C-it-DU-it is superior to C-it in improving uptake of all four ANC tests as measured by the proportion of women who received testing and management of HIV, syphilis, malaria and anaemia.To determine if C-it-DU-it is superior to C-it in improving uptake of HIV prevention services as measured by the proportion of women who received testing and management for HIV in the third trimester or at delivery, and the proportion of HIV-exposed infants with negative HIV PCR DNA tests at 6–8 weeks postpartum.

### Inclusion and exclusion criteria for pregnant women

2.9

The trial population will consist of pregnant women, regardless of age, who are resident within the catchment areas of trial sites for the duration of their pregnancy (and the trial period) and have delivered recently (within the preceding 8 weeks), who are willing to participate and provide written informed consent. Women enrolled in other interventional studies targeting pregnant women will be excluded.

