#### Participant screening

2.9.1

Trial data clerks and fieldworkers will screen women for eligibility at delivery at the maternity wards, post-natal clinics, child welfare clinics, female adult wards, gynaecology wards and outpatient clinics to allow capture of adverse pregnancy outcomes and early pregnancy losses. Trial fieldworkers will conduct home visits to screen eligible women who delivered at home or in non-study sites within the first 8 weeks post pregnancies. Trial data clerks will contact participants when the follow-up window opens (6–8 weeks post pregnancy) to minimise loss to follow-up.

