### Analytical plan/statistical methods

2.12

The intention-to-treat analysis population will consist of all eligible recruited participants who consented to participate in the trial from all randomised clusters. The per-protocol analysis populations will be those eligible, recruited and consented whose clusters had full implementation after WIT training on “analysing and using data to innovate” was completed within the expected timelines (Figure 2). These WITs will have determined a problem statement, developed a change plan, implemented it and tracked the relevant indicators in their monthly meetings.

No formal interim analysis will be carried out due to the long period between exposure to intervention and outcome ascertainment, and because this study does not test a direct patient-level intervention. The Institutional Review Boards (IRBs), the DMC and the Trial Steering Committee (TSC) will review study enrolment, progress and any safety concerns arising while the study is ongoing. Therefore, we will not define a stop criterion for this trial based on interim analyses. Instead, the trial will be stopped due to any major safety concerns, including direct harm to participants, as agreed upon by the IRBs, DMC and TSC.

We will conduct the primary analysis on the intention-to-treat population (ITT) using a binomial multilevel (random effects) model with a logit-link for estimation after which risk ratios (RR) and 95% confidence intervals will be estimated using parametric bootstrap procedures. This model was chosen as directly estimating RR is less robust, because RR may vary for reasons other than the magnitude of the effect because it is a ratio of two posterior probabilities, both of which are dependent on baseline prevalence of an outcome (22).

We will incorporate the facility (cluster) as a random effect and estimate *P*-values using parametric bootstrap procedures. We will assume the structure of the variance–covariance matrix for the random effect to be exchangeable. We will use similar methods of analysis to obtain crude and adjusted proportions for secondary outcomes and estimate standard errors of effect estimates while accounting for cluster-level correlation in all analyses.

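### The entry rule requires a delivery, yet early losses are screened for and miscarriage is an endpoint component; the rule and the primary endpoint's assessment time need reconciling

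*Protocol article*

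**What the plan says.** Five places in the protocol article bear on this.

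- **Eligibility (section 2.9).** Women resident in a trial catchment area qualify if they "have delivered recently (within the preceding 8 weeks), who are willing to participate and provide written informed consent". No other state of pregnancy is named.
- **Screening (section 2.9.1).** The list of places to screen ends with "gynaecology wards and outpatient clinics to allow capture of adverse pregnancy outcomes and early pregnancy losses". The same section times home visits and follow-up from the end of pregnancy rather than from delivery.
- **Adverse-outcome endpoint (section 2.8.2).** This is a "composite of foetal loss (stillbirth or spontaneous miscarriage), low birth weight or neonatal mortality".
- **Primary endpoint (section 2.8.1).** "The primary endpoint will be the proportion of pregnant women attaining at least eight ANC contacts", counted over facility and community contacts and "assessed at birth (or within the first 6–8 weeks for home births". No minimum length of pregnancy is set.
- **Analysis population (section 2.12).** "The intention-to-treat analysis population will consist of all eligible recruited participants who consented to participate in the trial from all randomised clusters". The primary analysis uses this population.

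**The concern.** The entry rule and the screening rule describe different populations. If a miscarriage is not a delivery, the women sought in gynaecology and outpatient clinics cannot be enrolled, and one named component of a secondary endpoint has nobody in it. If they are enrolled, they sit in the denominator of an endpoint that a short pregnancy leaves almost no chance of reaching, and the stated assessment time never arrives for them.

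The second reading matters most if the arms differ in how many losses they recruit. The trial is open-label and women are recruited after the pregnancy has ended. The Discussion (section 4) itself foresees that more antenatal attendance in the intervention arm could raise detection of adverse pregnancy outcomes without a true rise in risk. The article treats this as a limit on interpretation. Under the broad reading it would also add near-certain non-events to the intervention arm's primary denominator.

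**Working it through.** **1. The plan's own sample size.** Inputs from section 2.8.1: 3% vs 12%, ICC 0.025, 90% power, alpha 0.05 (taken here as two-sided), 8 clusters of 64 per arm.

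- Design effect: 1 + (64 − 1) × 0.025 = 2.575.
- The two-proportion formula with continuity correction gives 200 per arm; 200 × 2.575 = 515 per arm, or 1,030 in total, against 1,024 stated.
- Power for 8 × 64 per arm, unpooled variance, t reference with 14 degrees of freedom: 0.895.
- 1,024 × 18/16 = 1,152, and 1,152 / 0.80 = 1,440.

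The figures reproduce, so the sample size is not at fault.

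**2. The two readings.**

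- *Entry rule taken literally:* miscarriages are ineligible. A stillbirth is a delivery, so stillbirth, low birth weight and neonatal death remain observable. Only the miscarriage component is lost.
- *Entry rule read with sections 2.9.1 and 2.8.2:* early losses are eligible and enter the intention-to-treat population. Nothing in the article removes them from the primary denominator. The rule against imputing outcomes in section 2.12 concerns incomplete mother and child health books, and the book of a woman with an early loss may be complete.

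**3. Equal capture.** Let f be the share of analysed women whose pregnancy ended too early for eight contacts, all counted as non-events. The article gives no value; 5 to 15% is assumed. Each observed proportion is p(1 − f), so the risk ratio does not change. Power uses 9 clusters of 64 per arm, ICC held at 0.025, and a t reference with 16 degrees of freedom:

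noncentrality = (p2 − p1) / √{[p1(1 − p1) + p2(1 − p2)] × 2.575 / 576}

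At f = 0: 0.0291 + 0.1056 = 0.1347; √(0.1347 × 2.575 / 576) = 0.0245; 0.09 / 0.0245 = 3.67; power 0.931.

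| f (assumed) | Control | Intervention | Difference (points) | Risk ratio | Power, all women | Power, losses left out |
|---|---|---|---|---|---|---|
| 0 | 3.00% | 12.0% | 9.00 | 4.00 | 0.931 | 0.931 |
| 5% | 2.85% | 11.4% | 8.55 | 4.00 | 0.917 | 0.926 |
| 10% | 2.70% | 10.8% | 8.10 | 4.00 | 0.901 | 0.921 |
| 15% | 2.55% | 10.2% | 7.65 | 4.00 | 0.882 | 0.915 |

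The last column keeps 3% vs 12% and shrinks the cluster to 64(1 − f).

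**4. Unequal capture.** Observed risk ratio = 4.00 × (1 − f in intervention) / (1 − f in control). All splits are assumed.

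| Control losses | Intervention losses | Observed rates | Risk ratio | Difference (points) |
|---|---|---|---|---|
| 2% | 5% | 2.94% vs 11.40% | 3.88 | 8.46 |
| 3% | 8% | 2.91% vs 11.04% | 3.79 | 8.13 |
| 5% | 10% | 2.85% vs 10.80% | 3.79 | 7.95 |

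More losses recruited in the intervention arm pull the ratio towards 1. The reverse split, 10% control and 5% intervention, would give 4.00 × 0.95 / 0.90 = 4.22.

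**The case against.** The best defence is that *delivered* is loose wording in a condensed article. Section 2.9.1 sits under the eligibility heading, names early losses as a target and counts time from the end of pregnancy, so the intended meaning is fairly clear. Field staff work from the full protocol, which is not shown. That stands as far as it goes: nobody can say from the article that sites have enrolled different populations. It does not remove the mismatch, because the criterion as published still excludes women whom two other sections depend on.

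Three stronger readings are tempting, and the article does not support them.

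- *The foetal-loss endpoint cannot be assessed.* It can; only its miscarriage part is affected.
- *Women with losses are scored as failures on skilled birth, week-six immunisation and similar endpoints.* The article says no such thing. Denominators of secondary endpoints are commonly left to the SAP, and section 2.8.3 already uses one specific to an endpoint (HIV-exposed infants). Any spurious deficit computed for those outcomes would rest on an unstated scoring rule and unsourced rates.
- *The primary analysis should be confined to births and the 1,440 target counted in births.* That conditions the main comparison on reaching birth, a post-randomisation event that the trial itself treats as an outcome, and re-basing the target amounts to enrolling more women. Analysing all recruited women is a defensible choice.

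It is also fair to say that a woman for whom the assessment time never arrives might be regarded as not assessable rather than as a non-event. The article does not settle which, and that is part of the point.

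**Conclusion.** The inconsistency is in the text and should be resolved, but its likely numerical effect on the primary result is modest. Either the miscarriage component is unobservable, or early losses enter the primary denominator without an assessment time that fits them.

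The size cannot be derived from the article. Under equal capture, and assuming that every early loss is a non-event, the risk ratio stays at 4.00. Power falls from 0.931 to between 0.917 and 0.882 for 5 to 15% losses, and is still about 0.90 at 10%. Under the assumed unequal splits with more losses in the intervention arm, the risk ratio falls to between 3.79 and 3.88. The risk worth guarding against is unequal capture between open-label arms, not dilution as such.

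**What to change.** - Reword section 2.9 so that eligibility covers women whose pregnancy ended, by birth or loss, in the previous 8 weeks. This brings it into line with sections 2.8.2 and 2.9.1.
- State in section 2.8.1 when the primary endpoint is assessed for a pregnancy that ended in loss.
- Keep the primary analysis on all recruited women. Add a sensitivity analysis of the primary endpoint restricted to women with a live birth or stillbirth.
- Report the number of recruited losses by arm, so that unequal capture can be seen.
- Confirm in the SAP that skilled birth attendance uses births, and week-six immunisation uses live infants, as denominators.

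The cost is small. Pregnancy outcomes are already collected (sections 2.10.1 and 2.10.4), so no new data are needed, and the 1,440 target stays. Section 4.2 has recruitment running to February 2026; if it has closed, the rule actually applied can be recorded before database lock. The downside is that the sensitivity analysis conditions on reaching birth and uses slightly fewer women, which is why it should not replace the primary analysis.
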